In the non-cleft literature, several promising intervention programs exist for children at risk of poor language and academic outcomes. For example, parent-focused interventions to increase the frequency and quality of shared reading have improved children’s language and literacy skills. Dialogic book-sharing (DBS) is one example, emphasizing children’s active engagement in reading by using a child-directed approach, reflecting and encouraging child verbalizations, and encouraging conversational turns [13]. Because DBS emphasizes child language versus text (e.g., the books used often have few words and instead tell stories through illustration), it is appropriate for caregivers with a wide range of literacy [13–16]. Meta-analytic studies suggest that DBS programs lead to robust improvements in parents’ reading behaviors (d ~ 1.0) and moderate improvements in child language outcomes (d ~0.4) [13]. Though the format of these programs varies (e.g., 1:1 meetings with parents, group intervention), benefits have been observed with low-intensity, low-duration interventions (e.g., 90 minutes or more of direct intervention with caregivers). Most of these studies have been conducted with children who are typically developing. However, some evidence supports the efficacy of similar approaches with children who have language delays or are at risk for language delays [14]. Benefits are observed regardless of families’ socioeconomic status (SES), race and ethnicity, and language(s) spoken in the home [15].

Book Sharing for Toddlers with Clefts (BOOST) will be the first large study to examine the efficacy of an intervention to improve early language skills for children with CP±L. The current standard-of-care (SOC) for children with clefts includes developmental monitoring, assessment, and treatment of speech-language concerns. Based on research in non-cleft samples, there is good evidence that parent-focused programs can improve the frequency and quality of shared reading [13–16]. These programs have downstream effects on children’s language (particularly expressive and receptive language), which, in turn, predicts reading acquisition. We have focused our intervention on DBS models to promote frequent interactive parent-child reading.

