### Sample size considerations and participant recruitment and retention

We determined the sample size (N = 320) based on the number of participants needed to ensure 80% power to test the hypothesis that children in the BOOST intervention group will have better receptive and expressive language skills than those in the SOC comparison group. Power analyses were based on two-sample unequal-variance t-tests, an alpha = 0.05/2 to adjust for multiple comparisons, and up to 20% attrition (i.e., final N~256). Under these assumptions, we will have 80% power to detect treatment group differences of >0.4 SD for our primary outcomes. Treatment effects this large have been observed in DBS studies with other non-cleft populations and are considered plausible and clinically meaningful [13].

Our assessment of longitudinal changes in child language during book-sharing interactions (Hypothesis 1b) will use a generalized estimating equations (GEE) approach to linear regression with robust standard error estimates. The outcome for these analyses will be observed child language, calculated as an average number of utterances, unique words used, and mean length of utterance. Analyses will test the effects of the intervention on children’s language during book-sharing interactions over the five observations. We will have > 80% power to detect changes with an effect size > 0.4 between any two time points and changes with effect sizes > 0.3 overall. Meta-analyses of similar interventions with non-cleft participants suggest that effect sizes this large or larger are observed and considered clinically meaningful. Similarly, we will have > 80% power to assess longitudinal changes in children’s language during book-sharing interactions, the quality and frequency of book-sharing interactions, and changes in parents’ book-sharing behaviors as a mediator of differences in children’s language outcomes.

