### Randomization

Half the participants will be randomly assigned to the BOOST Intervention Group (n = 160). The other half of the participants (n = 160) will be randomized to a SOC comparison group that receives the same children’s books, uploads shared reading videos, and responds to surveys but does not receive individualized BOOST intervention sessions. Randomization will be stratified by study site, families’ preferred language (English or Spanish), and Medicaid status. Randomization will be blocked in blocks of 4 to 6 participants to ensure reasonable balance in small strata.

A data manager will prepare randomization lists for all sites using REDCap under the direction of the study biostatistician. These lists will be concealed from all other study staff. Once a patient has been determined eligible for participation and randomization, the site coordinator will enter the participant into the study database and receive the treatment assignment via REDCap.

Staff completing outcomes assessments (e.g., observational coding of parent-child interactions, child language assessments) will be unaware of group assignments. Masking will not be feasible for some procedures that, by definition, reveal participants’ group assignment (e.g., observational measures of treatment fidelity). We will use restrictions on user privileges in REDCap to limit access to this information in project databases, and we will use password/code protections to restrict access to calendars, data archives used to store videos, and any other information that might reveal group randomization. Masked staff will not participate in meetings where group assignments may be revealed. If an assessor or observational coder becomes aware of a participant’s group assignment, we will identify another staff member to complete the assessment/coding.

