We will use a multi-step linear regression approach to examine whether changes in parents’ reading behaviors mediate differences in children’s language outcomes. Mediators include: (1) shared reading frequency, (2) overall quality of parent-child interactions, and (3) parents’ shared reading skills, which will be assessed throughout the intervention period. Mediators will be analyzed separately to determine their individual effect on child outcomes and to avoid a washout effect from including all mediators in a single model. We will not adjust for multiple comparisons for this aim. Each regression model will follow the same basic approach to analyzing the effects of adjustment for a given mediator (Z) on the association between the intervention (X) on the child language outcome (Y). We will run two models per outcome: (1) Y = α + βX + e1, and (2) Y = A + BX + CZ + e2. The terms e1 and e2 represent model errors. Model 1 describes the unadjusted effect of the intervention on the outcome. Model 2 illustrates the combined effect of intervention and mediator on outcome. A comparison of the coefficients β and B indicates the degree of mediation. For example, β = B >0 suggests a positive intervention effect that is not mediated by Z (i.e., the null hypothesis of no mediation), whereas β >0 and B = 0 reflects a positive effect fully mediated by Z. Intermediate values reflect the degree of mediation (e.g., B = β/2 represents 50% mediation). Confidence intervals for the degree of mediation will be obtained using the bootstrap methods.

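### The claim of more than 80% power for mediation carries no conditions, and the interval planned for the degree of mediation has less power than an interval for β − B from the same bootstrap samples

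*Protocol article*

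**What the plan says.** The abstract of the protocol article makes mediation by the frequency and quality of shared reading the second of two primary hypotheses.

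The section on sample size considerations sizes the trial on the group comparison: "80% power to detect treatment group differences of >0.4 SD for our primary outcomes", with "up to 20% attrition (i.e., final N~256" participants analysed. It then states power for longitudinal change in observed child language, with effect sizes of 0.4 and 0.3. The closing sentence begins "Similarly, we will have > 80% power to assess longitudinal changes" and ends with "changes in parents’ book-sharing behaviors as a mediator of differences in children’s language outcomes". No share mediated, arm effect on the mediator, mediator-outcome association or alpha is attached to that last item.

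Statistical methods fits Y on arm (coefficient β), then Y on arm and mediator (arm coefficient B). It calls β = B the null hypothesis of no mediation, and gives B = β/2 as an example of 50% mediation. It then says: "Confidence intervals for the degree of mediation will be obtained using the bootstrap methods". There is no multiplicity adjustment for this aim.

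The Introduction reports meta-analytic effects from the non-cleft literature: "reading behaviors (d ~ 1.0) and moderate improvements in child language outcomes (d ~0.4".

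**The concern.** A power figure for mediation means little without the share mediated and the arm effect on the mediator. For a fixed share of a fixed total effect, a larger arm effect on the mediator implies a smaller mediator-outcome coefficient, which is harder to detect. An unconditional figure above 80% hides this.

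The choice of summary matters too. The degree of mediation, (β − B)/β, is a ratio whose denominator is itself estimated. Bootstrap samples with β near or below zero produce extreme or sign-reversed ratios, so the interval for the ratio can include zero when the interval for β − B does not. The plan's null concerns β − B, yet the only interval it names is for the ratio.

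At stake is how one of the two primary hypotheses is read. If an interval that includes zero is set beside a published claim of more than 80% power, a real but partial mediation could be taken as evidence of none.

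**Working it through.** **Inputs from the article.** 256 analysed, 128 per arm under 1:1 allocation; total effect 0.4 SD; mediator effect d = 1.0 as a background figure; models and bootstrap interval as in Statistical methods.

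**Assumptions.** Shares mediated of 25% and 50% (50% is the article's illustration, 25% is assumed); mediator effects of 0.7 and 0.5 as a range; two-sided alpha 0.05; unit within-arm variances; mediator measured without error; percentile bootstrap, since no type is named.

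**1. The plan's own figures.** SE(β) = √(2/128) = 0.125, so β is expected at 0.4/0.125 = 3.2 SE. At alpha 0.025 the power is Φ(3.2 − 2.24) = 83% (82.7% with the t distribution), so the primary sizing reproduces. The mediation figure cannot be recomputed, because its inputs are not given.

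**2. Ceiling on the ratio.** At alpha 0.05 the power for β itself is Φ(3.2 − 1.96) = 89%. In simulation the ratio interval levels off there: 89% at 75% mediated and 89% at 100% (d = 1.0).

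**3. Closed-form check on β − B.** The mediator coefficient is c = share × 0.4/d, with SE(c) ≈ √((1 − c²)/253). The arm effect on the mediator has z = d/0.125. Power is approximately the product of the two powers.

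- d = 1.0, 25%: c = 0.10, SE 0.0626, z = 1.60, power Φ(−0.36) = 36%.
- d = 1.0, 50%: c = 0.20, SE 0.0616, z = 3.25, power 90%.
- d = 0.7, 25%: c = 0.143, SE 0.0622, z = 2.30, power 63%.
- d = 0.5, 25%: c = 0.20, z = 3.25, power 90%; the arm-mediator path has z = 4.0 and power 98%; product 88%.

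At d = 1.0, 80% power needs z = 2.80, so c ≈ 0.173 and the share is 0.173/0.4 ≈ 43%.

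**4. Simulation.** The model was Y = (0.4 − c·d)X + cZ + error, with bootstrap resampling within arm. Power is the proportion of 95% intervals excluding zero.

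| Mediator d | Share mediated | Interval for (β − B)/β | Interval for β − B |
|---|---|---|---|
| 1.0 | 25% | 30% | 36% |
| 1.0 | 45% | 71% | 83% |
| 1.0 | 50% | 78% | 89% |
| 0.7 | 25% | 55% | 64% |
| 0.7 | 50% | 89% | >99% |
| 0.5 | 25% | 75% | 88% |
| 0.5 | 50% | 89% | 97% |

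**5. Sensitivity at d = 1.0.** A bias-corrected interval for the ratio gives 34% at 25% mediated and 82% at 50%. With no attrition (160 per arm) the ratio interval gives 40% and 91%. With mediator reliability 0.8 and 50% mediated, power is 74% for the ratio and 83% for β − B; at 45% mediated the β − B figure is 73%. At d = 1.3 and 50% mediated, the ratio interval gives 60% and the β − B interval 69%.

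**The case against.** The strongest reply is that no arithmetic error has been shown. The article gives no inputs from which its figure could be recomputed, any power claim fails at a small enough effect, and a journal article may leave supporting assumptions to the full protocol. The 25% share is not in the article. The d of about 1.0 comes from non-cleft studies of reading behaviours in general and is not a planning value for the three mediators. Controls here also receive books, record videos and answer surveys, so a smaller contrast is plausible, and power is then higher. The article also never says that mediation will be declared only if the ratio interval excludes zero. All of this stands. It is why 30% is one scenario and not the power of the design.

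The reply does not remove two facts. The figure is stated without any condition, although plausible inputs move it from about 30% to about 89%. And the only interval named is for the quantity with less power.

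A reader might infer three stronger things that the article does not support. The first is that the power claim is a miscalculation; without inputs that cannot be shown. The second is that the design falls short at 50% mediation. The 77% to 79% found there across runs is borderline, and power exceeds 80% with a bias-corrected interval, with the interval for β − B, or with no attrition. The third is that β lies so close to zero that the ratio is unusable. It is expected at about 3.2 SE, so the ratio loses power but remains reportable.

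**Conclusion.** The point holds as a conditional power claim stated unconditionally, together with an avoidable loss of power from the chosen summary. At 25% mediated, the planned interval has about 30%, 55% and 75% power for mediator effects of 1.0, 0.7 and 0.5; the β − B interval has about 36%, 64% and 88%. The gain from using β − B was 6 to 13 points in every partial-mediation scenario run.

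The figures rest on 128 per arm, a 0.4 SD total effect, alpha 0.05, a percentile bootstrap and an error-free mediator. Measurement error in the mediator would lower them. Low power at 25% mediated with d = 1.0 held under every workable interval tried (30% to 37%) and without attrition (40% to 44%).

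**What to change.** 1. In Statistical methods, base the test of β = B on the bootstrap interval for β − B, in SD units. Report the degree of mediation as a descriptive ratio with its own interval.
2. In the sample size section, attach conditions to the mediation power. For example: with the β − B interval, 128 per arm, two-sided alpha 0.05 and an error-free mediator, power exceeds 80% if about 45% or more of a 0.4 SD effect is mediated and the mediator effect is d = 1.0; a smaller share suffices at smaller d (at d = 0.5, 25% gives about 88%), and a larger share is needed if the mediator is measured with error.

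The models, data and bootstrap samples are unchanged, as is the sample size. The cost is a change of wording and a less favourable, conditional power statement.

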### Recruitment and retention

Collectively, participating centers see approximately 200 new patients with isolated clefts each year. We anticipate a 50% consent rate, allowing us to enroll our target sample with up to 4-years of recruitment. Sites will complete ongoing reviews of medical records to identify potentially eligible participants in our target age range. Study flyers will be made available in the clinic, and information will be shared among cleft team providers, such as nurses, speech-language pathologists, psychologists, social workers, pediatricians, geneticists, and surgeons, so they can also inform families about possible participation. We will approach potentially eligible participants in the clinic or by phone when children are 24 to 32 months old. Parents who express interest will complete a brief interview, in person or by telephone, to confirm eligibility. In addition to receiving children’s books in their preferred language, families will receive incentives for completing study activities for sending shared reading videos ($40 per video shared) and completing the final evaluation ($150). We will also provide the results of children’s end-of-study language assessments in a brief report and encourage parents to share the results with their child’s pediatrician and other providers.

Study visits will be scheduled at times convenient for participating families to facilitate retention. We will use multiple strategies to communicate with families, including text and e-mail reminders for study visits. Participants will be considered "lost to follow-up" if they cannot be contacted, do not respond to outreach attempts, or cannot schedule their child’s outcome assessment within six months of the end of the intervention or active participation (controls). To minimize attrition, we will ask families for the name and contact information of an alternate contact who could help us locate them. We will also use formal and informal search strategies (e.g., online white page searches, Omnitrace) to find families as needed. We will make at least four attempts to contact families using several modes of contact, such as phone, letter, text, and e-mail. Our sample size of N = 320 provides adequate power to address the study aims with 20% attrition.

### Randomization

Half the participants will be randomly assigned to the BOOST Intervention Group (n = 160). The other half of the participants (n = 160) will be randomized to a SOC comparison group that receives the same children’s books, uploads shared reading videos, and responds to surveys but does not receive individualized BOOST intervention sessions. Randomization will be stratified by study site, families’ preferred language (English or Spanish), and Medicaid status. Randomization will be blocked in blocks of 4 to 6 participants to ensure reasonable balance in small strata.

A data manager will prepare randomization lists for all sites using REDCap under the direction of the study biostatistician. These lists will be concealed from all other study staff. Once a patient has been determined eligible for participation and randomization, the site coordinator will enter the participant into the study database and receive the treatment assignment via REDCap.

Staff completing outcomes assessments (e.g., observational coding of parent-child interactions, child language assessments) will be unaware of group assignments. Masking will not be feasible for some procedures that, by definition, reveal participants’ group assignment (e.g., observational measures of treatment fidelity). We will use restrictions on user privileges in REDCap to limit access to this information in project databases, and we will use password/code protections to restrict access to calendars, data archives used to store videos, and any other information that might reveal group randomization. Masked staff will not participate in meetings where group assignments may be revealed. If an assessor or observational coder becomes aware of a participant’s group assignment, we will identify another staff member to complete the assessment/coding.

### Data management

We plan to use direct entry into centralized REDCap databases to reduce the use of paper record forms and data entry steps. Before enrolling participants, staff involved in data entry will pilot test databases with sample record forms to ensure accuracy and assess any database issues that need to be addressed. Regular study coordinator teleconferences will address questions throughout the study and ensure continuity across centers. All data entry forms and databases will be password protected, with access restricted depending on staff roles/responsibilities. The study team and data entry staff will ensure that data entry is accurate and complete. Seattle Children’s Research Institute staff will run monthly reports to identify missing data with logic checks to assess potential data entry errors. The investigator or designee will review unanticipated problems and adverse events.

### Statistical methods

In analyses for our primary outcomes, we will use an intention-to-treat (ITT) approach to test the hypothesis that children in the BOOST group exhibit better language skills than children in the SCO comparison group. We will calculate 2-sample unequal-variance t-tests to estimate treatment versus control group differences in child language outcomes post-intervention. We will calculate standardized treatment effect sizes (ES) for all analyses to allow comparison across outcomes with different measurement scales. We will not adjust for covariates in the primary analyses. However, in sensitivity analyses, we will use bias-corrected ITT analyses to examine the robustness of treatment effects in the setting of non-adherence, missing data, or study attrition. To assess attrition bias, we will explore outcomes using Inverse Probability Weighting (IPW), with weights determined by the probability of having missing data or being lost to follow-up based on the RCT stratification variables and demographic and clinical data [39]. We will also conduct sensitivity analyses to examine the effects of variation in treatment fidelity using a weighting approach. Finally, we will examine the potential effects of children’s participation in other interventions in the community (e.g., speech and language therapy) using censored normal regression (CNR) [40].

Longitudinal analyses examining changes in child language during book-sharing and caregiver behaviors (i.e., quality and frequency of book-sharing) will use a GEE approach to linear regression with robust standard error estimates. This approach accounts for the correlation of observations over time and allows for the use of partial data on subjects who are lost to follow-up or non-compliant. Estimates will be adjusted for the RCT stratification variables, demographic confounds, and clinical characteristics (e.g., cleft type, age at cleft repair). Smoothing splines will be fit to examine changes in parents’ reading behaviors over time, including non-linear trends.

We will use a multi-step linear regression approach to examine whether changes in parents’ reading behaviors mediate differences in children’s language outcomes. Mediators include: (1) shared reading frequency, (2) overall quality of parent-child interactions, and (3) parents’ shared reading skills, which will be assessed throughout the intervention period. Mediators will be analyzed separately to determine their individual effect on child outcomes and to avoid a washout effect from including all mediators in a single model. We will not adjust for multiple comparisons for this aim. Each regression model will follow the same basic approach to analyzing the effects of adjustment for a given mediator (Z) on the association between the intervention (X) on the child language outcome (Y). We will run two models per outcome: (1) Y = α + βX + e1, and (2) Y = A + BX + CZ + e2. The terms e1 and e2 represent model errors. Model 1 describes the unadjusted effect of the intervention on the outcome. Model 2 illustrates the combined effect of intervention and mediator on outcome. A comparison of the coefficients β and B indicates the degree of mediation. For example, β = B >0 suggests a positive intervention effect that is not mediated by Z (i.e., the null hypothesis of no mediation), whereas β >0 and B = 0 reflects a positive effect fully mediated by Z. Intermediate values reflect the degree of mediation (e.g., B = β/2 represents 50% mediation). Confidence intervals for the degree of mediation will be obtained using the bootstrap methods.

Finally, we will explore demographic and clinical characteristics associated with "good" versus "poor" treatment responses. In these analyses, we will examine parent reading behaviors and child outcomes in relation to clinical and demographic characteristics (e.g., language spoken in the home, family composition, parents’ education level, the child’s cleft type, child’s hearing status, sex of the child, study center/interventionists). We will use a two-step process for model selection and analysis. First, we will identify children who score > 0.5 SD above or below the mean relative to their intervention group. Second, we will examine the distribution of each characteristic of interest and identify those that (a) differ in distribution between those who score above-expected values, below-expected values, and as-expected and (b) have sufficient cell sizes (n >30). Selected variables will then be included in multivariate linear regression models to evaluate whether parents’ reading behaviors and child language outcomes vary across subgroups. We will calculate correlations between each variable before fitting any model, combining or excluding variables to avoid multicollinearity. To prevent overfitting, no more than 12 terms will be included in the model.

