#### Child language during book-sharing

We will transcribe book-sharing interactions using the video recordings shared by parents throughout the study. Child vocalizations will be coded for the number of clear and intelligible utterances, the number of unique words used, and the mean length of utterance (MLU).

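### The primary comparison, labelled intention-to-treat, uses only children with a final assessment, and the attrition check as described names none of the language data recorded from those who leave

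*Protocol article*

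**What the plan says.** All points are from the protocol article.

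- **Primary test** (Statistical methods): "We will calculate 2-sample unequal-variance t-tests to estimate treatment versus control group differences in child language outcomes post-intervention". The approach is called intention-to-treat, and covariates are excluded.
- **Analysed number** (Sample size considerations): the calculation allows for "up to 20% attrition (i.e., final N~256".
- **Timing** (Table 1): the expressive and receptive one-word tests and the language sample are taken only at the final assessment, weeks 16 to 40.
- **Attrition check** (Statistical methods): bias-corrected ITT sensitivity analyses are announced without further description. Inverse probability weights are to be "based on the RCT stratification variables and demographic and clinical data".
- **Language recorded earlier**: CDI-CAT is a scheduled baseline measure (Caregiver report measures; Table 1). At least one reading video is required before randomisation (Eligibility criteria). Videos 2 to 5 fall in weeks 2 to 8 (Table 1). On the coding of child language the article says: "We will transcribe book-sharing interactions using the video recordings shared by parents throughout the study".
- **Use of partial data** (Statistical methods): mentioned only for the longitudinal GEE models.

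**The concern.** A Welch test on observed final scores estimates the effect in all randomised children only if, within each arm, loss is unrelated to the outcome. The arms differ in what could drive loss. BOOST families have three individual sessions with feedback on their videos; SOC families have none. A family whose child is progressing slowly may therefore leave at different rates, or for different reasons, in each arm.

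The best recorded evidence of how a lost child was doing is the child's own language before the family left. The weights as described rest on characteristics that do not measure progress, so they can confirm a biased estimate as robust. At stake is a shift that could be a sizeable fraction of the target effect, in a direction that cannot be known in advance.

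**Working it through.** **1. The plan's own figure.** 320 × (1 − 0.20) = 256, or 128 per arm. With two-sided alpha 0.05/2 = 0.025 (sidedness is not stated; two-sided assumed), 0.4 SD and 80% power:

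n per arm = 2(2.241 + 0.842)² / 0.4² ≈ 119; total after loss = 2 × 119 / 0.8 ≈ 298.

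At 128 per arm, power is 83.1% (normal) or 82.7% (t), and the detectable difference is 0.385 to 0.387 SD. The stated 80% at 0.4 SD is slightly conservative and is not at issue. It does show that up to 320 − 256 = 64 randomised children are expected to be absent from the primary test.

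**2. Bias of the observed-case mean.** If a fraction d of an arm is lost and leavers lie g SD below their arm mean, the mean of those who remain is too high by

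bias = d / (1 − d) × g.

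If loss depends on week-8 language, g = ρ × m. Here ρ is the video-outcome correlation and m is the leavers' shortfall in week-8 language. Logistic selection on a standard normal variable, integrated numerically, gives m. Loss in the other arm is taken as unrelated to language. ρ and the odds ratios are assumptions; the article gives neither.

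| Loss | Odds ratio per SD | m | d/(1−d) | Bias at ρ = 0.4 | 0.6 | 0.7 |
|---|---|---|---|---|---|---|
| 20% | 2 | 0.515 | 0.250 | 0.052 | 0.077 | 0.090 |
| 20% | 3 | 0.742 | 0.250 | 0.074 | 0.111 | 0.130 |
| 10% | 2 | 0.596 | 0.111 | 0.026 | 0.040 | 0.046 |

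The sign is positive if slower children leave BOOST and negative if they leave SOC. With 20% loss, ρ = 0.6 and odds ratios of 2 and 1.5 in the two arms, the net bias is 0.25 × 0.6 × (0.515 − 0.316) = 0.030 SD. With equal odds ratios it is 0.

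**3. What each correction leaves.** Simulation with 20% loss, selection on week-8 language in BOOST only, log-odds slope 1.0 per SD (odds ratio about 2.7), and correlations of the final score with baseline and on-study language of 0.6 each:

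| Analysis | Bias (SD) |
|---|---|
| Observed cases | 0.108 |
| Weights on demographic and clinical data | 0.105 |
| Weights adding baseline language | 0.073 |
| Weights or arm-wise imputation adding on-study language | 0.006 |

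A second set of assumptions (baseline-outcome correlation 0.5, video-outcome 0.6, baseline-video 0.5) gives the same pattern. Arm-wise imputation from baseline language alone reduces 0.077 to 0.046 SD at odds ratio 2, and 0.111 to 0.067 SD at odds ratio 3. Adding week-8 language brings both to about 0.

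**4. Error rate.** With 160 per arm, no true effect and nominal 2.5%, the t-test rejects in 2.4% of trials under random loss. Under selection on on-study language in one arm it rejects in 4.5% (slope 0.5) and 8.2% (slope 1.0).

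**5. Limit of any such correction.** If loss depends on the unseen final score itself (slope 1.0), the observed-case bias is 0.17 to 0.18 SD. Between 0.07 and 0.11 SD remains after all recorded language is used.

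**The case against.** The plan does address attrition: it names bias-corrected ITT analyses and weighting for missing data. An article condenses, and the full list of weight variables may stand in an analysis plan that is not shown. Clinical data is a category that could include CDI-CAT. Retention is taken seriously: non-adherent children are still offered the final assessment, and there are payments, alternate contacts and at least four contact attempts. Stopping sessions or videos is thus not the same as missing the outcome. The bias needs selection that differs by arm. The standard error of the difference is √(2/128) = 0.125 SD, so 0.077 SD is about 0.6 of a standard error. Some leavers will have stopped uploading before week 8, and the one-word tests have no earlier measurement, so video codes serve only as proxies. An observed-case primary analysis with a weighted sensitivity analysis is a recognised choice.

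Much of this stands and limits the size and certainty of the point. It does not remove it. The article itself fixes the test, the absence of covariates and the kinds of data behind the weights, and its own examples of clinical characteristics in the same section are cleft type and age at repair. Even the generous reading, with baseline language included, leaves 0.073 of 0.108 SD in the simulation above.

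A reader might infer that the trial will overstate the BOOST effect, that the plan ignores missing data, or that using the videos would make the estimate unbiased. The documents support none of these. They give no evidence of differential loss or its direction, they do plan attrition analyses, and the near-zero residual holds only when loss depends on language that was recorded.

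**Conclusion.** The point holds in conditional form. As specified, the primary test is an observed-case analysis under an intention-to-treat label, and the attrition check as described names no language measure. If selection on language progress differs between arms, the estimate is biased either way by about 0.05 to 0.09 SD (roughly 13% to 22% of the 0.4 SD target) at 20% loss, odds ratio 2 in one arm and none in the other, and correlations of 0.4 to 0.7. Twenty per cent is the article's upper figure for loss; the correlations and odds ratios are assumed. Weights on demographic and clinical data alone leave nearly all of this bias. They would suffice if loss depended only on those variables.

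This does not show that the observed-case test is invalid or must be abandoned. It shows that relevant data, already scheduled for collection and coding, are left out of the stated safeguard.

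**What to change.** Specify that the missing-data analysis covers all randomised children and uses, by arm, baseline CDI-CAT, age, the stratification factors and every available video language code (utterances, unique words, mean length of utterance).

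- **Preferred:** multiple imputation by arm followed by the same Welch comparison, as the primary estimate.
- **Minimum:** keep the t-test as primary and add these variables to the weighting model.
- **In either case:** describe the t-test on observed scores as an observed-case analysis, and add a delta-based (tipping-point) analysis, since no model on recorded data removes loss that depends on the unseen final score.

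The cost is revised wording, modest programming and reliance on an imputation or weighting model. No new data are needed. Enrolment is to run to about April 2028 and no interim outcome analyses are planned, so the change can be fixed in advance of any comparison between arms.
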